### Data collection methods

2.12

All outcome measures will be collected via self-report questionnaires completed electronically by participants through the LimeSurvey platform at three time points: baseline (Time I, 24–30 weeks of gestation), post-intervention (Time II, 34–37 weeks of gestation), and postpartum (Time III, ≥6 weeks after delivery). No investigator-administered measurements will be performed. The data collection schedule is presented in Table 2.

To promote data quality, the LimeSurvey platform has been configured to prevent submission of incomplete questionnaires, to flag out-of-range responses, and to present items in a fixed order. All questionnaire links will be sent directly to participants via secure electronic communication. Data will be entered automatically into a password-protected database accessible only to the research team.

The following validated instruments will be used:

#### Time I—prenatal assessment

2.12.1

The following instruments will be utilised for data collection during pregnancy:

Custom Prenatal Questionnaire (Part A): A self-report form designed to collect sociodemographic and clinical background information.Iowa Infant Feeding Attitude Scale (IIFAS) (54), Polish adaptation (55): A 16-item self-report scale used to assess women’s attitudes and beliefs towards breastfeeding and formula feeding, to predict the choice of feeding method and intended duration of breastfeeding. The Polish adaptation demonstrated acceptable psychometric properties in a sample of 401 postpartum women, with satisfactory internal consistency (Cronbach’s *α* = 0.725), confirmed two-factor structure accounting for 31.18% of variance, and discriminative power coefficients above 0.2 for all items. Subscales were strongly correlated with the total score (*r* = 0.803 for both subscales) (55).Multidimensional Scale of Perceived Social Support (MSPSS) (56), Polish adaptation (57): A 12-item self-report tool for measuring perceived social support from three sources: family, friends, and a significant other. The Polish adaptation demonstrated satisfactory psychometric properties in a sample of 1,322 adults, with confirmed three-factor structure (RMSEA = 0.065; *χ^2^*/df = 2.957) and high internal consistency (Cronbach’s *α* = 0.893 for the total score; *α* = 0.931 for Friends; *α* = 0.915 for Family; *α* = 0.865 for Significant Other), as well as satisfactory temporal stability and convergent validity (57).Pregnancy-Related Anxiety Questionnaire—Revised 2 (PRAQ-R2), Polish adaptation (26). The primary outcome measure, the PRAQ-R2, is a 10-item questionnaire that covers three subscales of anxiety specific to pregnancy and childbirth: (1) fear of childbirth, (2) worries that the child will be physically or mentally disabled, and (3) concern about one’s own appearance during pregnancy. The overall and factor scores demonstrate good reliability and validity regardless of parity. The Polish adaptation of the PRAQ-R2 demonstrated good psychometric properties in a sample of 175 Polish pregnant women. Confirmatory factor analysis confirmed the original three-factor structure (CFI = 1.00; TLI = 1.00; RMSEA < 0.001), and internal consistency was satisfactory across all subscales and the total score (Cronbach’s *α* ranging from 0.68 to 0.94). Convergent validity was confirmed through significant correlations with the Hospital Anxiety and Depression Scale (HADS) and the Visual Analogue Scale (VAS) (26).Patient Health Questionnaire-4 (PHQ-4), Polish version: A short questionnaire used in screening in primary healthcare practice and clinical settings for examining anxiety and depressive symptoms. The Polish version demonstrated good psychometric properties in a large community sample of Polish adults (*n* = 1,115), with acceptable internal consistency (Cronbach’s *α* = 0.74 for the anxiety subscale and *α* = 0.77 for the depression subscale), confirmed two-factor structure, and measurement invariance across age and gender groups (58).Post-Traumatic Stress Disorder Questionnaire (PTSD-8), Polish (59): The PTSD-8 questionnaire contains questions about stress reactions manifested as intrusion (four items), avoidance (two items) or hyperarousal (two items). It is both a diagnostic tool for PTSD and an assessment tool to evaluate the severity of this syndrome, its determinants and health consequences. The Polish adaptation demonstrated high reliability (Cronbach’s α = 0.891, McDonald’s *Ω* = 0.890) and acceptable construct validity based on confirmatory factor analysis of an adjusted single-factor model (CMIN/DF = 4.944; NFI = 0.976; RFI = 0.955; IFI = 0.981; TLI = 0.964; RMSEA = 0.073, 90% CI: 0.057–0.090). Factor loadings ranged from 0.613 to 0.760, and average variance extracted (AVE) was 0.489 (59).

#### Time II—post-intervention assessment

2.12.2

The second phase of data collection will consist solely of a follow-up measurement using the PRAQ-R2 to assess changes in the primary outcome.

#### Time III—postpartum assessment

2.12.3

The following instruments will be utilised for data collection after delivery:

Custom Postpartum Questionnaire (Part B): a self-report form designed to collect supplementary interview data and clinical information following childbirth.Perinatal Post-Traumatic Stress Disorder Questionnaire-II (PPQ-II), Polish translation (60, 61): a 14-item self-report questionnaire assessing childbirth-related PTSD symptoms across two domains: Avoidance/Intrusion and Arousal. The Polish adaptation demonstrated very good psychometric properties in a sample of 273 postpartum mothers, with high internal consistency (Cronbach’s *α* = 0.92 for the total score; *α* = 0.91 for Avoidance/Intrusion; *α* = 0.86 for Arousal), confirmed two-factor structure explaining 62% of total variance (KMO = 0.90), good convergent validity with the PTSD-8 (*r* = 0.43–0.85) and DASS-21 (*r* = 0.54–0.78), and excellent temporal stability over a 3-month interval (*r* = 0.90) (61)MSPSS: as described above (Time I) (57)Birth Satisfaction Scale-Revised (BSS-R), Polish (62, 63)PHQ-4: As described above (Time I) (58)

To promote retention, reminder messages will be sent prior to each data collection time point, and research midwives will maintain contact with participants throughout the study period. Participants who discontinue the intervention but remain willing to complete follow-up assessments will be encouraged to do so. Where possible, outcome data from participants who withdraw will be retained for intention-to-treat analysis. Reasons for withdrawal and loss to follow-up will be recorded and reported.

### Data management

2.13

All data will be collected electronically via LimeSurvey and stored in a secure database accessible only to the research team. Participants will be identified by anonymous study ID numbers; the linkage file will be stored separately and accessible only to the principal investigator. Data will be checked for completeness and out-of-range values prior to database lock. All study data will be retained for a minimum of 10 years on the institutional servers of the Medical University of Gdańsk, in accordance with GDPR. Anonymous data may be shared upon reasonable request, subject to approval by the principal investigator and the Bioethics Committee.

### Statistical analysis plan

2.14

Analyses will be conducted according to randomised group allocation and will primarily follow the intention-to-treat principle, insofar as outcome data are available. The primary endpoint is PrA measured using the PRAQ-R2 at 34–37 weeks’ gestation. The primary analysis will compare post-intervention PRAQ-R2 scores between groups using analysis of covariance (ANCOVA), with treatment group as the main factor and baseline PRAQ-R2 score as a covariate. The primary outcome is assessed at two prenatal time points only: baseline and post-intervention. The postpartum assessment applies exclusively to secondary outcomes.

Secondary outcomes will be analysed using regression models appropriate to outcome type, with logistic regression for binary outcomes and linear regression for continuous outcomes. Secondary analyses will be considered supportive and exploratory; no formal adjustment for multiplicity is planned. Missing data will be described by study arm and time point. The primary analysis assumes data are missing at random (MAR); this assumption will be examined via sensitivity analysis, using a mixed-effects model for repeated measures applied to all available longitudinal data. Multiple imputation is not planned. The possibility of data missing not at random (MNAR) cannot be excluded and is acknowledged as a limitation. Stratification variables included in the randomisation will be entered as covariates in the primary ANCOVA model. A supportive per-protocol analysis will also be conducted among participants with observed primary endpoint data; in the intervention arm, this will additionally require completion of at least four intervention sessions. Two pre-specified sensitivity analyses will be conducted: (1) a linear mixed-effects model including midwife as a random effect, to account for potential clustering by intervention deliverer; and (2) a mixed-effects model for repeated measures applied to all available longitudinal data under a missing-at-random assumption, to assess the robustness of findings in the presence of incomplete data.

The mode of intervention delivery (in-person versus remote) will be recorded. As the trial is not powered for formal moderator analyses, any comparison by delivery mode will be considered exploratory and interpreted cautiously.

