#### Criteria for discontinuing or modifying the intervention

2.5.4

The intervention may be discontinued or modified for an individual participant in the following circumstances: withdrawal of informed consent at any point during the trial; emergence of a severe psychiatric condition requiring specialist treatment (e.g., acute psychosis, severe depressive episode); clinically significant deterioration in psychological wellbeing as assessed by the delivering midwife and confirmed by the principal investigator; initiation of pharmacological treatment for anxiety or depression during the trial period; obstetric complications requiring hospitalisation or precluding participation; preterm birth prior to completion of the intervention; or inability to continue participation due to unforeseen personal circumstances.

In cases of discontinuation, the participant will be referred to appropriate clinical or psychological services where indicated. All outcome data collected prior to discontinuation will be retained and included in the intention-to-treat analysis. Participants who discontinue the intervention but remain willing to complete follow-up assessments will be encouraged to do so.

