### Harms

2.7

Given the non-invasive nature of the intervention, no serious adverse events are anticipated. An adverse event is defined as any unintended negative psychological or physical experience reported by a participant during or following a session, including clinically significant increases in anxiety or acute emotional distress. Adverse events will be monitored by the delivering midwife at each session using the standardised session log and reported to the principal investigator within 24 h. Participants experiencing clinically significant deterioration will be referred to appropriate services in accordance with the safety protocol described in section Criteria for Discontinuing or Modifying the Intervention.

In cases where a participant develops severe anxiety, acute distress, or suicidal ideation, the delivering midwife will immediately notify the principal investigator, discontinue participation, and refer the participant to specialist psychiatric services. All such events will be reported to the Bioethics Committee of the Medical University of Gdańsk.

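### The mixed model said to examine the missing-at-random assumption itself assumes it and, with one post-baseline PRAQ-R2, cannot show lack of robustness to departures from it

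*Protocol article*

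**What the plan says.** All statements on missing data are in section 2.14 of the protocol article. The primary model is an ANCOVA of the Time II PRAQ-R2 "with treatment group as the main factor and baseline PRAQ-R2 score as a covariate", valid under MAR. Of that assumption the section says "this assumption will be examined via sensitivity analysis, using a mixed-effects model for repeated measures applied to all available longitudinal data". When it lists the two sensitivity analyses it describes the second as the same repeated-measures mixed model, "applied to all available longitudinal data under a missing-at-random assumption". It rules out multiple imputation, promises a description of missing data by arm and time point, and concedes as a limitation that data may be missing not at random (MNAR). No MNAR analysis is planned.

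On how much data the model has, section 2.14 says "The primary outcome is assessed at two prenatal time points only: baseline and post-intervention". Section 2.12.2 adds "The second phase of data collection will consist solely of a follow-up measurement using the PRAQ-R2", and Table 2 agrees.

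Two places bear on why Time II may be missing. For severe anxiety, acute distress or suicidal ideation, section 2.7 says that the delivering midwife "will immediately notify the principal investigator, discontinue participation, and refer the participant to specialist psychiatric services". Section 2.5.4 says "Participants who discontinue the intervention but remain willing to complete follow-up assessments will be encouraged to do so", and section 2.12.3 repeats this.

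**The concern.** A sensitivity analysis for a missing-data assumption has to vary that assumption. This one keeps it, so the plan's only check of MAR cannot do the job that the text gives it. The practical risk lies in reporting: the two analyses will agree, or differ for unrelated reasons, and readers will be told that MAR was examined.

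Informative loss is foreseeable here. Only intervention women are seen session by session by a delivering midwife, so the section 2.7 rule for acute distress can be triggered at sessions in that arm alone. If distressed intervention women are the ones without a Time II score, the available-case ANCOVA overstates the benefit.

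**Working it through.** The plan gives no figure on this point to reproduce. The check concerns what the model can see, and then how large a departure could matter.

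**Inputs.** From section 2.9: planned difference 3.27, SD 8.56, 31 per group needed, 37 per group recruited, a 20% allowance for dropout and incomplete outcomes. From sections 2.12.2 and 2.14 and Table 2: one baseline and one post-baseline PRAQ-R2 in the analysis. Section 2.14 does not fix how baseline enters the mixed model or which covariance structure is used, so each form is taken in turn. Write Y1 for baseline, Y2 for Time II, g for arm.

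**1. Baseline as covariate.** A woman without Y2 has no response row. The model is the complete-case ANCOVA.

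**2. Baseline as response, common baseline mean, unstructured covariance.** The likelihood factors as f(Y1) × f(Y2 | Y1, g), with E(Y2 | Y1, g) = a + τg + bY1. A woman without Y2 contributes to f(Y1) only, which does not contain τ. The estimate of τ is therefore the complete-case ANCOVA estimate. In 300 simulated trials the largest difference was 2 × 10⁻⁷ points, under both ML and REML.

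**3. Baseline as response, separate baseline means by arm, unstructured covariance.** The same factorisation gives

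- Time II contrast = τ + b × D
- change contrast = τ + (b − 1) × D

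where τ and b are the complete-case ANCOVA estimates and D is the baseline difference between arms among all women randomised. In one simulated trial D = 1.3766 and τ = −4.1607. The Time II contrast was −3.3416, a difference of 0.8191, so b = 0.8191 / 1.3766 = 0.595. The change contrast should then be −4.1607 + (0.595 − 1) × 1.3766 = −4.718, which is what the fit gave. The extra term is baseline imbalance and would appear with no missing data at all. Over the 300 trials the differences reached 2.5 points (Time II contrast) and 1.6 points (change contrast), but averaged only 0.02 and −0.04. The Time II difference correlated 0.96 with D.

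**4. Compound symmetry.** Forcing equal variances at both times also moves the estimate: up to 2.6 points in one trial, 0.07 to 0.14 on average in absolute size.

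**5. Does any form detect MNAR?** The 300 trials had 37 per arm, 6 of 37 missing per arm (1 − 31/37 = 16.2%), baseline restricted to scores of 30 or more, and residual SD 8.56 × 0.8 = 6.85. Loss was random in control, and more likely with high Time II scores in the intervention arm. The slope of 0.6, the residual SD factor of 0.8 and the strength of the MNAR mechanism are assumptions.

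| Analysis | Mean effect |
|---|---|
| ANCOVA on full data | −3.08 |
| Complete-case ANCOVA | −4.32 |
| Mixed-model forms (range) | −4.29 to −4.45 |

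The bias was 4.32 − 3.08 = 1.24 points, and no form removed it. In the forms that can differ from the ANCOVA, the difference was uncorrelated with the MNAR bias (−0.08 to +0.02).

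**6. Size of a departure.** If a fraction f of the intervention arm is missing and those women score δ worse than MAR predicts, the effect shrinks by about f × δ. Every δ is an assumption.

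| f | δ | Shift | Left of 3.27 |
|---|---|---|---|
| 10% | 5 | 0.50 (15%) | 2.77 |
| 20% | 5 | 1.00 (31%) | 2.27 |
| 16.2% | 4.28 (0.5 SD) | 0.69 | 2.58 |
| 20% | 4.28 (0.5 SD) | 0.86 | 2.41 |
| 16.2% | 8.56 (1 SD) | 1.39 | 1.88 |
| 20% | 8.56 (1 SD) | 1.71 | 1.56 |

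With departures in both arms the shift is the difference of the two products. Equal loss and equal δ cancel.

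**The case against.** The strongest reply is that the form of the mixed model is left open, so a reader who infers that it must reproduce the ANCOVA estimate in every case goes too far. That is right: steps 3 and 4 show visible single-trial differences. It does not rescue the check, because those differences carry no information about departures from MAR. A fuller analysis plan that fixed the form would not change this either.

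A reader might also infer that nothing in the plan would reveal informative loss. The documents do not support that. Missing data will be described by arm and time point, reasons for withdrawal and loss will be recorded and reported (sections 2.5.5 and 2.12.3), and MNAR is openly named. An excess of distress-related loss in one arm would be seen. What is absent is any measure of its effect on the result.

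Third, section 2.5.2 and Table 1 schedule another PRAQ-R2 at the last completed session, in the intervention arm only. If it entered the mixed model, the estimate could change. Section 2.14 restricts the primary outcome to two time points, so the natural reading leaves it out. If it were included, it would inform one arm only and the model would still assume MAR.

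Finally, the 5-point departure exceeds the planned effect, is placed in one arm in one direction, and has no source in the documents. It shows scale and is not a forecast.

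**Conclusion.** The point holds in this form: the model that section 2.14 offers as an examination of MAR assumes MAR and cannot show lack of robustness to departures from it. This rests on the document's own wording and on the single post-baseline PRAQ-R2, and not on the simulation. Exact equality with the complete-case ANCOVA is limited to the baseline-adjusted forms in steps 1 and 2. The primary ANCOVA itself is not faulted. The possible effect of a departure runs from about 0.5 to 1.7 points of the planned 3.27 over the table above, all under assumed departures confined to the intervention arm.

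The wording of sections 2.7 and 2.5.4 is a lesser matter. It is tempting to call it a flat contradiction. However, section 2.5.4 speaks of stopping the intervention and section 2.7 of stopping participation in a narrower group, and it is unclear whether participation includes the questionnaires.

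**What to change.** 1. In section 2.14, delete the statement that the mixed model examines the MAR assumption. If the model is kept, describe it as another MAR analysis, and do not report its agreement with the ANCOVA as robustness to departures from MAR.
2. Add, or substitute for sensitivity analysis 2, a delta-adjusted tipping-point analysis of the primary ANCOVA. Shift the predicted Time II scores of women with missing data over a pre-specified range (for example 0 to +10 points in steps of 2), in the intervention arm alone and in both arms, and report the shift at which the conclusion changes.
3. Use a variance that reflects the missing data: an analytic mean-score variance, or multiple imputation for this sensitivity analysis only. Do not fill in single predicted values and rerun the ANCOVA as if they were observed. In a simulation with 37 per arm and 7 missing per arm (assumed slope 0.6, residual SD 6.85), that gave a mean standard error of 1.43 against an empirical 1.79 at zero shift, 20% too small (1 − 1.43/1.79), and 1.58 against 1.83 at +10. The tipping point would be misplaced.
4. Reconcile section 2.7 with sections 2.5.4 and 2.12.3 on whether follow-up questionnaires are still sought from women whose participation is discontinued for safety. Which way is for the investigators to decide.

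The cost is a change of wording and a little extra analysis work, with no new data. With the analytic variance, the decision against multiple imputation can stand. The change should be made before unblinding.

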#### Secondary outcomes

2.6.2

Anxiety and depressive symptoms will be assessed using the PHQ-4 total score (range 0–12) and two subscale scores: PHQ-2 for depressive symptoms (items 1–2; cut-off ≥3) and GAD-2 for anxiety symptoms (items 3–4; cut-off ≥3). The metric is the change from baseline (Time I) to postpartum assessment (Time III, ≥6 weeks postpartum), with mean scores compared between groups.

Childbirth-related PTSD symptoms will be assessed prenatally using the PTSD-8 total score (range 0–24; no universally established cut-off in the original instrument) at baseline (Time I), and postnatally using the PPQ-II total score and subscale scores at Time III. Mean final values will be compared between groups.

Childbirth satisfaction will be measured using the BSS-R total score at Time III, with mean final values compared between groups.

Perceived social support will be assessed using the MSPSS total score (range 12–84) and three subscale scores (Significant Other, Family, Friends; range 4–28 each) at baseline (Time I) and postpartum (Time III), with mean scores compared between groups.

Infant feeding attitudes will be measured using the IIFAS total score at baseline (Time I) and reported descriptively.

Mode of birth and obstetric outcomes will be collected via the Custom Postpartum Questionnaire (Part B) at Time III and reported as frequencies and proportions.

Although all instruments will be administered in full, not all subscales or total scores will be analysed within the scope of this trial; some data will be reserved for secondary research questions and future analyses. Detailed descriptions of all measurement instruments, including psychometric properties of Polish adaptations, are provided in section 2.12 Data Collection Methods. Formal permissions for the use of all Polish adaptations have been obtained from the respective copyright holders prior to the commencement of the study.

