### Sample characteristics and size

2.9

Sample size planning was informed by the Polish validation study of the PRAQ-R2, from which an anticipated 10% reduction in the mean score (3.27 points) and variability estimates for repeated measurements were derived. In this two-group randomised trial, the primary comparison will be the between-group difference in post-intervention PRAQ-R2 adjusted for baseline score, analysed using a two-sided significance level (*α*) of 0.05. Based on these assumptions, G*Power 3.1 indicated a minimum of 31 participants per group to achieve 80% statistical power. It should be noted that no MCID has been established for the PRAQ-R2 (26, 38). The 3.27-point planning assumption was derived from 10% of the Polish normative mean and additionally verified against distribution-based criteria: the anticipated difference approximates 0.5 SD of the total score [SD ≈ 8.56; (38)], a widely accepted proxy for minimal important difference in the absence of anchor-based estimates. This limitation is acknowledged; the present trial will contribute effect size data to inform future MCID derivation.

Because this is the first evaluation of an intensive, individually delivered midwife-led psychoeducational intervention in this setting, the final recruitment target of 74 women (37 per group) was retained as a pragmatic sample size balancing methodological considerations and intervention deliverability. The study is intended to provide an initial estimate of treatment effect and variance, and to inform the design of a future larger trial. An additional 20% was incorporated into the recruitment target to account for anticipated dropout, loss to follow-up, and incomplete outcome data (52, 53).

To achieve this, approximately 500 women will be screened in the second trimester to identify the eligible cohort with elevated PRAQ-R2 scores. This estimate reflects the expected prevalence of elevated PrA in the target population—a Polish pilot study found that approximately 56% of low-risk pregnant women scored ≥30 points on the PRAQ-R2 (26), combined with additional attrition anticipated from non-response, incomplete questionnaire completion, failure to meet remaining eligibility criteria, and non-consent prior to randomisation. Sample size planning was performed using G*Power 3.1.

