### Randomisation and blinding

2.11

Allocation to study groups at a 1:1 ratio will be performed using block randomisation with variable block sizes, computer-generated by a researcher not involved in recruitment. Allocation concealment will be ensured through sequentially numbered, opaque, sealed envelopes. The recruiting midwife will open the next consecutive envelope only after obtaining the participant’s final informed consent. Blinding of participants and intervention-delivering midwives is not feasible given the nature of the psychoeducational programme, consistent with standard practice in behavioural RCTs. Since all outcome questionnaires are self-completed via a secure online platform, no assessor is present at any data collection time point, which substantially mitigates assessment bias. The researcher responsible for data management and the data analyst will both be blinded to group allocation throughout the analysis phase, using coded group labels. Unblinding will only occur if authorised by the principal investigator for safety or ethical reasons and will be formally documented.

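### Postpartum PHQ-4 and MSPSS should be adjusted for their own baseline scores, a free gain in precision; separately, the strata sentence in the primary model has no counterpart in the randomisation

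*Protocol article*

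**What the plan says.** **Secondary outcomes.** For PHQ-4, section 2.6.2 (Secondary outcomes) states: "The metric is the change from baseline (Time I) to postpartum assessment (Time III, ≥6 weeks postpartum), with mean scores compared between groups". For MSPSS, the same section lists Time I and Time III measurements and says that group means are compared, without saying whether this means change or the postpartum value. The childbirth PTSD outcome uses two instruments, PTSD-8 at Time I and PPQ-II at Time III, compared on final values. BSS-R is postpartum only. IIFAS is measured at baseline only and is descriptive. Table 2 confirms that PHQ-4 and MSPSS are the only secondary scales measured at both times.

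Section 2.14 (Statistical analysis plan) assigns linear regression to continuous secondary outcomes and logistic regression to binary ones. It lists no covariates for them and calls these analyses supportive and exploratory.

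**Primary model.** Section 2.14 specifies ANCOVA with group as the factor and baseline PRAQ-R2 as covariate, and section 2.9 also describes a baseline-adjusted comparison. Section 2.14 then adds: "Stratification variables included in the randomisation will be entered as covariates in the primary ANCOVA model". The randomisation itself is described only in section 2.11 (Randomisation and blinding), as "block randomisation with variable block sizes, computer-generated by a researcher not involved in recruitment", with consecutively numbered sealed envelopes. No stratification factor is named there or elsewhere.

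**The concern.** Section 2.14 names a baseline covariate for the primary outcome and none for the secondary outcomes. If the PHQ-4 sentence is taken at face value, the analysis is a comparison of mean change. A change score subtracts the whole baseline value, including its measurement noise, and is less precise than regression on baseline. When the baseline–follow-up correlation is below 0.5, it is less precise even than ignoring baseline. For MSPSS, comparing postpartum means would ignore a baseline score that the trial already holds.

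At stake is precision in a trial of 37 women per arm. PHQ-4 bears on the depressive-symptom part of H2. Social support is not named in H2.

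The strata sentence is a separate and smaller matter. It points to variables that the description of the randomisation does not contain, so a reader cannot tell whether section 2.11 omits something or section 2.14 carries a redundant line.

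**Working it through.** **Inputs.** The article gives no figure for the precision of PHQ-4 or MSPSS and no baseline–follow-up correlation r for either, so r = 0.3, 0.5 and 0.7 are assumptions. The number analysed is taken as 31 per arm, from "G*Power 3.1 indicated a minimum of 31 participants per group to achieve 80% statistical power", with two-sided α = 0.05. The recruitment target of 37 is about 31 × 1.2 = 37.2.

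The figure of 31 serves here only as a number analysed. It belongs to the primary outcome, and it does not follow from the printed difference of 3.27 and SD of 8.56 alone. Without baseline adjustment these give 2 × (1.960 + 0.842)² × (8.56/3.27)² ≈ 108 per group. ANCOVA gives 31 only at r of about 0.845. The article does not print the correlation it used, so this does not show 31 to be wrong, and it is a separate matter.

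**PHQ-4: adjusted analysis against unadjusted change.** With the same SD σ at both times:

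- variance of change = 2σ²(1 − r)
- residual variance after baseline adjustment = σ²(1 − r²)
- ratio = (1 − r²) / [2(1 − r)] = (1 + r)/2

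| assumed r | variance ratio | SE ratio | SE reduction | 1/variance ratio |
|---|---|---|---|---|
| 0.3 | 0.65 | 0.81 | 19% | 1.54 |
| 0.5 | 0.75 | 0.87 | 13% | 1.33 |
| 0.7 | 0.85 | 0.92 | 8% | 1.18 |

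The last column is the factor by which the sample would have to grow for an unadjusted change score to match the adjusted analysis.

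The direction does not depend on equal SDs. With SDs σ₁ and σ₃ at Times I and III, the variance of change minus the adjusted variance is σ₁² − 2rσ₁σ₃ + r²σ₃² = (σ₁ − rσ₃)², which cannot be negative.

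**Detectable difference.** With 31 analysed per arm and 80% power, an unadjusted final score detects √(2/31) × (1.960 + 0.842) = 0.712 SD. Multiply by √[2(1 − r)] for change and by √(1 − r²) for the adjusted analysis:

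| assumed r | change | adjusted |
|---|---|---|
| 0.3 | 0.84 SD | 0.68 SD |
| 0.5 | 0.71 SD | 0.62 SD |
| 0.7 | 0.55 SD | 0.51 SD |

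**MSPSS.** If the comparison is of unadjusted Time III means, the variance ratio is 1 − r²: 0.91, 0.75 and 0.51 at the same assumed r. The square roots are 0.95, 0.87 and 0.71, so the SE is about 5%, 13% and 29% smaller. If change is meant, the PHQ-4 table applies.

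**Strata.** No arithmetic applies. Section 2.11 describes blocks of variable size and a single consecutive run of envelopes, and names no strata. Section 2.14 admits to the primary model only variables used in the randomisation. If there were none, that set is empty and the model is group plus baseline PRAQ-R2, as 2.14 and 2.9 already say. If there were some, section 2.11 is incomplete.

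**The case against.** The strongest reply on the secondary outcomes is that nothing in the article excludes baseline adjustment. Linear regression can carry the Time I score, and regressing change on group plus baseline gives the same treatment effect as ANCOVA. The outcome wording does not settle the model either. Section 2.6.1 describes the primary outcome as change with means compared between groups, yet section 2.14 analyses it by baseline-adjusted ANCOVA. This stands. A reader might infer that all secondary outcomes with a baseline are compared as raw change and that adjustment is lost. The article does not support that: only PHQ-4 is defined as change, and the covariates are unstated rather than ruled out. What remains is that one sentence would settle the matter at no cost.

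It also stands that these analyses are declared exploratory, that the correlations are assumed, and that the gain for PHQ-4 shrinks as r rises.

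On the strata, a reader might infer that the primary model is stated in two incompatible ways, or that its covariates could be chosen after the data are seen. Neither follows. The sentence admits only variables fixed at randomisation, before outcome data exist, and baseline PRAQ-R2 stays in the model in every case. Nor is the absence of stratification by parity an error; that is a design preference. The mismatch between the two sections does remain. It is not easily put down to condensation, because the article says that the full protocol and analysis plan are published within it.

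**Conclusion.** This is a free improvement on exploratory outcomes, plus a minor wording correction.

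Adjusting Time III PHQ-4 and MSPSS for their own Time I scores is at least as precise as comparing change or final means. For PHQ-4 against unadjusted change, the SE is about 8% to 19% smaller for r between 0.7 and 0.3. That gain is realised only if baseline would otherwise have been left out, and its size rests on assumed correlations and equal SDs at the two times. Its direction rests on neither.

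The strata sentence leaves a gap between sections 2.11 and 2.14 that should be closed. It does not undermine the primary analysis.

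**What to change.** 1. In sections 2.6.2 and 2.14, state that Time III PHQ-4 and MSPSS scores are analysed by linear regression on group, with the Time I value of the same scale as covariate. Subscales that are analysed should follow the same rule.
2. Adjusting PPQ-II for Time I PTSD-8 is optional, because they are different instruments. If it is wanted, say so in advance.
3. Reconcile sections 2.11 and 2.14. If the randomisation is stratified, name the factors in 2.11. If it is not, delete the sentence in 2.14, which leaves group and baseline PRAQ-R2 as the primary model.

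The cost is wording only. Both scales are already scheduled at Time I, and section 2.12 says that the survey platform blocks incomplete questionnaires, so adjustment should exclude few or no women. The change should be made before the analyst is unblinded.
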